# The effect of the TIM program (Transfer ICU Medication reconciliation) on medication transfer errors in two Dutch intensive care units: design of a prospective 8-month observational study with a before and after period

**DOI:** 10.1186/s12913-017-2065-y

**Published:** 2017-02-10

**Keywords:** Medication reconciliation, Medication error, Intensive care unit, Medication transfer, Clinical pharmacist, Adverse drug event

## Abstract

**Background:**

The transfer of patients to and from the Intensive Care Unit (ICU) is prone to medication errors. The aim of the present study is to determine whether the number of medication errors at ICU admission and discharge and the associated potential harm and costs are reduced by using the Transfer ICU and Medication reconciliation (TIM) program.

**Methods:**

This prospective 8-month observational study with a pre- and post-design will assess the effects of the TIM program compared with usual care in two Dutch hospitals. Patients will be included if they are using at least one drug before hospital admission and will stay in the ICU for at least 24 h. They are excluded if they are transferred to another hospital, admitted and discharged in the same weekend or unable to communicate in Dutch or English.

In the TIM program, a clinical pharmacist reconciles patient’s medication history within 24 h after ICU admission, resulting in a “best possible” medication history and presents it to the ICU doctor. At ICU discharge the clinical pharmacist reconciles the prescribed ICU medication and the medication history with the ICU doctor, resulting in an ICU discharge medication list with medication prescription recommendations for the general ward doctor. Primary outcome measures are the proportions of patients with one or more medication transfer errors 24 h after ICU admission and 24 h after ICU discharge. Secondary outcome measures are the proportion of patients with potential adverse drug events, the severity of potential adverse drug events and the associated costs.

For the primary outcome relative risks and 95% confidence intervals will be calculated.

**Discussion:**

Strengths of this study are the tailor-made design of the TIM program and two participating hospitals. This study also has some limitations: A potential selection bias since this program is not performed during the weekends, collecting of *potential* rather than *actual* adverse drug events and finally a relatively short study period.

Nevertheless, the findings of this study will provide valuable information on a crucial safety intervention in the ICU.

**Trial registration:**

Dutch trial register: NTR4159, 5 September 2013

## Background

Patients in the intensive care unit (ICU) are more likely to experience medication errors than other hospitalized patients, since the chance of errors in an ICU setting is high due to the high intensity of treatment in patients with a critical illness [1, 2]. Medication errors can induce adverse events and are associated with substantial costs [3–10]. It has been demonstrated that chronic medication used by patients before admission to the ICU is often unintentionally discontinued after the ICU stay [11]. Because of the critical illness, non-vital medication is often temporarily withheld. However when the patient improves, the restart of this medication is easily forgotten. On the other hand, drug therapy initiated for short-term use in the ICU can be inadvertently continued after ICU discharge. For example, several studies have demonstrated that gastric acid-inhibitory drugs are frequently continued inappropriately after discharge from the ICU [12–14].

On regular wards, many Dutch hospitals use computerized physician order entry systems with clinical decision support (CPOE/CDS). In general, these CPOE/CDS systems cannot offer supporting systems for patient monitoring required at ICUs. Therefore most ICUs in the Netherlands do not use the general CPOE/CDS system. Instead, they use a so-called Patient Data Monitoring System (PDMS). However, these systems mostly lack clinical decision support for prescribing and monitoring medication. Besides, the use of two different systems poses an additional threat to safe medication transfer to and from the ICU.

Various interventions have been studied to reduce medication errors on the ICU. A systematic review by Manias et al. identified eight types of interventions: implementation of CPOE, changes in working schedules, intravenous systems, modes of education, medication reconciliation, pharmacist involvement, protocols an guidelines and support systems for clinical decision making. Only four of these interventions demonstrated reduced medication errors post-intervention, one of which was medication reconciliation at ICU admission [15]. Besides, a small number of studies suggest that that the incidence of medication errors during and after hospitalization can be reduced even further by additional medication reconciliation at ICU discharge [16–18].

However, the effect of medication reconciliation after ICU stay is not well described in the literature. The few available studies suffer from one or more of the following limitations: (1) small sample size; (2) failure to differentiate between intentional and unintentional discrepancies and (3) lack of assessment of potential clinical impact and/or severity of discrepancies. Besides, it is not known how patient safety will be affected by a combined admission and discharge medication reconciliation program in the ICU.

In the present study, we hypothesize that continuity of care will be improved and medication errors and patient harm will be reduced if medication is reconciled during both ICU transfers by a pharmacist in close collaboration with the intensive care doctors and the ICU staff. To test this hypothesis, we designed the TIM (*T*ransfer *I*CU and *M*edication reconciliation) program, which consists of medication reconciliation by a pharmacist at ICU admission and at ICU discharge.

## Methods/Design

### Aim of the study

The aim of this study is to determine the effect of the TIM program on the number of medication transfer errors (MTEs) at admission to and at discharge from the ICU. Furthermore, we will investigate the effect of the program on the number of potential adverse drug events and their severity, and finally we will estimate the cost-effectiveness of this program.

### Design

A prospective 8-month observational study with a before and after design will be carried out at Haga Teaching Hospital in The Hague (650 bed general teaching hospital with 18 ICU beds; 1500 ICU admissions a year) and Erasmus Medical Center in Rotterdam (University Hospital, 1320 beds and 32 ICU beds; 1800 ICU admissions a year). Both hospitals are located in the Netherlands.

The study consists of three periods: first, a pre-intervention period of 14 weeks during which patients will be included who receive usual care; second, a period of 4 weeks during which the TIM intervention program will be implemented, and finally, a post intervention period of 14 weeks during which patients will be included in the TIM program (Fig. 1).

**Fig. 1 Fig1:**
[figure not shown]
Study flow chart of the TIM program and defined outcomes. ICU = intensive care unit, MTE = medication transfer error, pADE = *potential* adverse drug event, TIM = Transfer ICU and Medication reconciliation program

### Study population

All patients admitted to the ICU during the study period are eligible to participate in this study if they use at least one drug at home and if the ICU length of stay exceeds 24 h. An ICU discharge and readmission within 24 h is counted as one inclusion. Patients who die during the ICU stay are included in the admission part of the study. Readmissions to the ICU are also included.

Exclusion criteria are transfer to another hospital, both admission and discharge within the same weekend (Friday 17:00 until Monday 8:30) and patient’s inability to be counseled in Dutch or English.

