### Outcome measures

Figure 1 presents a summary of outcome measures.

The primary outcome measures of this study are the proportion of patients with one or more MTEs at admission to the ICU and the proportion of patients with one or more MTEs after discharge from the ICU.

An MTE at admission is defined as an unintentional discrepancy between BPMH and medication prescribed within 24 h after admission to the ICU.

An MTE at discharge is defined as an unintentional discrepancy between the BPML-GW24 and the medication chart of the patient within 24 h after discharge.

Whether a discrepancy at admission is unintentional or not is based on information documented in the PDMS, the ICU standards of care and the ICU pharmacist’s interpretation of the situation (see Fig. 4 for the assessment of unintended medication discrepancies).

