### Data analysis

#### Sample size

The primary outcome of this study is the proportion of patients with one or more transfer errors at admission to the ICU and at discharge from the ICU.

Based on literature the expected proportion of patients with medication errors due to transfer between wards within one hospital is 62% [18]. Based on a conservative interpretation of this study, it was estimated that this proportion is 30% in our study. With an estimated 50% reduction of errors due to the intervention, an alpha of 0.05 and a power of 0.80 the calculated sample size is 133. This sample size is based on patients being alive at discharge for both the pre-intervention as the post-intervention phase.

With an estimated mortality of 35%, in each measurement phase 205 patients should be included. Based on 1500 (Haga Teaching Hospital) and 1800 (Erasmus MC) admissions a year, an estimated loss of 30% due to the ICU stay less than 24 h and another 35% loss due to weekend ICU stay, we estimate a study period of 7 weeks for Erasmus MC and 8 weeks for Haga. To be on the safe side and to measure during a robust intervention period, we will double the number of calculated weeks. Therefore a pre- and post-intervention period of 14 weeks is chosen.

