#### Statistical analysis

All data will be entered in MS Access 2007 and will be analyzed with IBM SPSS Statistics 24.

Patients from the intervention and control group will be compared for all baseline characteristics using *t*-test for continuous normally distributed variables, Mann-Whitney *U*-test for continuous non-normally distributed variables and chi square test for categorical variables.

For the primary outcome (MTEs) relative risks and 95% confidence intervals will be calculated. As the study has a pre- and post-design, results will be corrected for potential confounders by using multivariate logistic regression analysis.

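### Later ICU readmissions count as further inclusions, yet the primary outcome is a proportion of patients and the named methods treat all inclusions as independent; the effect on the confidence intervals is small

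*Protocol article*

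**What the plan says.** Three parts of the protocol article bear on this.

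- **Study population** sets the inclusion unit: "An ICU discharge and readmission within 24 h is counted as one inclusion", and "Readmissions to the ICU are also included". The 24 h rule has a purpose only if a readmission after that window is a new inclusion.
- **Outcome measures** sets the outcome unit. The first primary measure is "the proportion of patients with one or more MTEs at admission to the ICU", and the second is the matching proportion after ICU discharge. The Sample size section repeats the patient as the unit and asks for 205 patients per phase, but it derives accrual from 1500 and 1800 ICU admissions a year.
- **Statistical analysis** names the methods: "For the primary outcome (MTEs) relative risks and 95% confidence intervals will be calculated", and "results will be corrected for potential confounders by using multivariate logistic regression analysis".

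The article does not limit the analysis to one stay per patient, redefine the unit as the stay, or say how repeat stays of one person are handled.

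**The concern.** If the text is followed literally, a patient who returns to the ICU after more than 24 h, and again meets the criteria, contributes two or more rows to what is reported as a proportion of patients. The reported quantity is then a proportion of stays.

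The rows of one patient are also likely to be positively correlated, because the home medication list is largely the same each time. An ordinary relative-risk interval or logistic model treats them as unrelated. The error bars are then wrong, in a direction that depends on where the repeat stays fall. At stake are the meaning of the primary proportion and the accuracy of its interval.

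**Working it through.** **Step 1. The plan's own figures.** Inputs from the Sample size section are 30% in the control phase, a 50% reduction (so 15%), alpha 0.05, power 0.80 and 35% mortality.

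- A two-sided comparison of two independent proportions needs 120.5 per phase without continuity correction and 133.5 with it. The stated 133 is the corrected figure.
- 133 / (1 − 0.35) = 204.6, so 205. This matches.

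Both figures treat every inclusion as an independent patient.

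**Step 2. Expected accrual.** Inputs from the same section are 1500 + 1800 = 3300 admissions a year, a 30% loss for short stays, a further 35% for weekend stays, and 14 weeks.

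- 3300/52 × 0.70 × 0.65 × 14 ≈ 404 inclusions per phase
- 404 × 0.65 ≈ 263 discharged alive

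These are counts of admissions, with no deduction for repeat patients.

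**Step 3. Repeat stays within a phase.** The documents give neither a readmission rate nor a correlation, so both are assumptions. Let s be the share of inclusions that are second stays in the same phase and ρ the within-patient correlation. A share 2s of the rows then lies in pairs:

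Design effect = (1 − 2s) + 2s(1 + ρ) = 1 + 2sρ

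The true standard error is the naive one times √(design effect). The true two-sided error of a nominal 5% test is 2[1 − Φ(1.96/√(design effect))].

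| s | ρ | Design effect | True SE / naive SE | Naive SE too small by | True error |
|---|---|---|---|---|---|
| 0.05 | 0.3 | 1.03 | 1.015 | 1.5% | 5.4% |
| 0.10 | 0.5 | 1.10 | 1.049 | 4.7% | 6.2% |
| 0.15 | 0.7 | 1.21 | 1.100 | 9.1% | 7.5% |

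**Step 4. Effect on the interval.** Take a relative risk of 0.50 (15% against 30%) and 263 per phase.

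SE of log RR = √[0.70/(263 × 0.30) + 0.85/(263 × 0.15)] = 0.174

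| Design effect | 95% CI | Power at 263 per phase |
|---|---|---|
| 1 (naive) | 0.355 to 0.704 | 98.6% |
| 1.03 | 0.353 to 0.707 | 98.4% |
| 1.10 | 0.349 to 0.716 | 97.7% |
| 1.21 | 0.343 to 0.728 | 96.5% |

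Power is computed without continuity correction at 263/(design effect). For the admission outcome, with about 404 inclusions per phase, it stays above 99% throughout.

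**Step 5. Patients with stays in both phases.** Here the correlation enters as a covariance that is subtracted from the variance of the before–after contrast. Let c be the share of stays in each phase that belong to a patient also seen in the other phase, with equal phase sizes. The variance of log RR is multiplied by 1 − kcρ, where

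k = 2√(V₀V₁)/(V₀ + V₁), V₀ = 0.70/0.30 = 2.333, V₁ = 0.85/0.15 = 5.667, so k = 0.909.

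Taking c = 0.05 and ρ = 0.5 as an illustration, the factor is 1 − 0.909 × 0.05 × 0.5 = 0.977. The naive standard error is then about 1.2% too large (1/√0.977 = 1.012). The sign is opposite to Step 3.

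**The case against.** The handling of repeated stays is routine content for an analysis plan, and that plan is not shown. The article's statistical section is short, names no variance estimator and does not rule out clustering. This is a fair point against saying that clustering was forgotten. It does not remove the conflict of units, because the inclusion rule and the outcome definition are both fixed in this text, and no variance method makes a count of stays into a proportion of patients.

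The readmission share is also unsupported and may be lower than assumed. A repeat stay must start after the 24 h window, itself exceed 24 h, avoid the weekend and transfer exclusions, and fall within the same 14 weeks. The correlation is uncertain too: the discharge gold standard draws partly on records of that particular ICU stay, and the admission list can take in ward and operating-room medication. The range is therefore illustrative.

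A reader might infer more than the documents support:

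- **That the intervals are too narrow overall.** This follows only for repeat stays within a phase. Step 5 gives the opposite sign for patients seen in both phases, and the documents do not say which dominates.
- **That the chi-square test is affected for the primary outcome.** The article names that test only for comparing baseline characteristics.
- **That readmissions should be left out, or contaminate the comparison because the reconciled list already exists.** Including them is a stated and defensible choice, since every transfer is an occasion for error. A list already on record can equally be seen as part of what the program does.
- **That a first-stay primary analysis would cure the problem.** Taking the first stay within each phase still leaves some people in both phases, and a patient treated during the 4-week implementation period may already have been reconciled.

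**Conclusion.** The point holds in a limited form. The inclusion rule counts stays, the primary outcome is worded in patients, and the methods as named make no allowance for several stays by one person. Separate counting of readmissions after 24 h is an inference from the merging rule, but no other reading fits.

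The consequence is modest. Under the assumed ranges for within-phase repeats, the standard error is about 1.5–9% too small and the true error about 5.4–7.5%; stays in both phases offset this in part. If the planned effect is seen, the conclusion does not change: even at a design effect of 1.21 the upper limit of the interval is 0.728. Power is not threatened at the expected accrual. The point is worth correcting because the unit of the primary outcome should be unambiguous, not because the study's result is in danger.

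**What to change.** - State the ICU stay as the primary unit, and use it consistently in the outcome definition, the sample-size text and the reporting.
- Compute the relative risk and the adjusted model with patient-clustered robust variance, or with GEE. The patient should be the cluster across both phases, so that the error bars are corrected in either direction.
- Report the number of patients and the number of stays in each phase.
- Add a sensitivity analysis restricted to each patient's first eligible stay.

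The cost is a few sentences of text, a patient identifier that links stays across phases, slightly more analysis work and possibly slightly wider intervals. The sensitivity analysis is affordable: even if 15% of inclusions were repeat stays, 404 × 0.85 ≈ 343 inclusions and 263 × 0.85 ≈ 223 survivors per phase would remain, against the 205 and 133 required.

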### Study procedures

#### Usual care at ICU admission (pre-intervention period)

At ICU admission the ICU doctors determine pre-admission medication. In this process, they rely on the data from the previous ward (if applicable), the patient’s general practitioner, relatives or previous hospital records (e.g. discharge letters, patient charts). Occasionally, a faxed medication list is available from the community pharmacy, but there is no standard procedure for the ICU doctor to obtain medication lists from the community pharmacy. Hence, ICU doctors do not structurally perform medication reconciliation. The admitting doctor registers pre-admission medication in the PDMS system (Haga) or HIS (Hospital Information System) (Erasmus MC) and only transcribes the medication that is to be continued during the ICU stay into the PDMS/CPOE

In Erasmus MC a dedicated ICU hospital pharmacist reviews the prescribed medication on the ICU on a daily basis during patient rounds. In Haga Teaching Hospital, twice a week, one out of a team of 4 trained ICU hospital pharmacists reviews prescribed medication and attends the patient rounds on the ICU. In both hospitals, the hospital pharmacists rely on the information about pre-admission medication available in the PDMS and do not obtain a medication list from the community pharmacy, nor do they reconcile pre-admission medication with the patient.

#### Usual care at ICU discharge

An ICU doctor writes an ICU discharge letter, which is screened, verified and authorized by an intensivist. Combined with a nurse discharge letter, this discharge letter is sent to the admitting ward at the moment of patient transfer.

In Haga Teaching Hospital, the discharge letter contains information about the registered pre-admission medication, the medication in use at discharge from the ICU and suggestions about medication use after discharge (i.e.: “Restart pre-admission medication”). In Erasmus MC, the letter contains information about medication in use at discharge and sometimes suggestions for medication use after discharge.

After transfer, the doctor of the admitting ward has to transcribe medication orders from the discharge letter to the hospital CPOE/CDS. At the same time, doctors in the Haga Teaching Hospital have to stop medication registered in the CPOE/CDS that the patient is no longer required to take after ICU discharge, since the CPOE/CDS system in this hospital does not automatically stop prescribed medication when the patient is admitted to the ICU. By contrast, the CPOE/CDS system in Erasmus MC stops all medication at admission to the ICU, which urges the doctor to prescribe all medication needed after the ICU transfer.

#### TIM program, the intervention

The TIM program consists of medication reconciliation at ICU admission and at ICU discharge. In both intervention hospitals, the program will be carried out by two pharmacists. The pharmacists in Erasmus MC will be supported by pharmacy students, who, after a training period of several weeks, will be able to collect the medication lists and to interview the patients or their relatives about each patient’s pre-admission medication.

#### TIM program at ICU admission

First, permission for reconciliation is obtained from the patients or their relatives. Next, the pharmacist compiles a best possible medication history (BPMH) as described below in the section “the gold standard medication lists”. In case of an internal transfer, the BPMH will also include the pre-admission medication transcribed or omitted at the previous ward.

Next, the pharmacist transfers the BPMH to the PDMS system (Haga) or HIS (Erasmus MC) and presents the BPMH to the ICU doctor responsible for the patient. If the pharmacist notices an inexplicable discrepancy between pre-admission medication and medication prescribed on the ICU, he or she will discuss this with the ICU doctor, enabling correction of unintended omissions or other mistakes in the ICU prescriptions. Finally, the pharmacist in Haga Teaching Hospital stops the patient’s medication in the CPOE/CDS system used on the wards, which is done automatically in the HIS system of Erasmus MC when the patient is admitted to the ICU.

#### TIM program at ICU discharge

When a patient is discharged from the ICU, the pharmacist makes a discharge medication summary. This medication summary contains an overview of medications on the patient’s BPMH combined with all the medication the patient uses in the ICU at the moment of discharge. For each drug, the ICU doctor is given a series of options of recommendations (i.e.: restart, stop, continue), making it easier for the ICU doctor to provide clear prescription suggestions to the doctor of the general ward. The ICU pharmacist reconciles this medication list with the ICU doctor. During this reconciliation, special attention is paid to temporarily withheld medication that should be restarted and to temporary ICU medication that should be stopped. After this reconciliation, the pharmacist amends the medication list to establish the Best Possible ICU Medication Discharge List (BPMDL-ICU) (example in Fig. 2). Once the doctor has approved the BPMDL-ICU, it is combined with the discharge letter of the ICU and sent to the doctor of the regular ward at the moment of patient transfer.

